**Table 1 Tab1:**
[figure not shown]
Standard Protocol Items: Recommendation for Interventional Trials (SPIRIT) diagram of assessments at enrolment, allocation, post-intervention, and 6-month-follow-up time points

*Abbreviations: ASQ* Affective Style Questionnaire, *BADS* Behavioral Activation for Depression Scale, *BDI*-*II* Beck Depression Inventory II, *CLS* Compassionate Love Scale, *FFMQ* Five Facet Mindfulness Questionnaire, *FSS* Social Pain Questionnaire, *IOS* Inclusion of Other in the Self Scale, *OFD* Operationalized Skills Assessment Inventory, *QIDS*-*C* Quick Inventory of Depressive Symptomatology, *RSQ*-*D* Response Styles Questionnaire, *SASS* Social Adaptation Self-evaluation Scale

The schedule of enrolment, interventions, and assessments is provided in Table 1.

### Data collection

Data from observer-rated measures will be collected by blinded, independent, trained clinical psychologists. The data will be logged on paper case report forms and afterwards independently entered by two project employees into a SPSS data sheet. All paper-based documents will be kept in a locked steel locker. Access to any data is restricted to trial personnel and investigators. The SPSS data sheet is stored on a secured server that is placed in a locked steel locker in a room accessible only by authorized IT personnel. The data values in the SPSS file are limited to appropriate ranges to ensure that only valid data are entered and will be checked for data entry mistakes.

Self-report measures, including all secondary outcomes except the OFD, will be collected by computerized questionnaires, using the academic online survey platform unipark [84]. The program ensures complete data entry. To ensure anonymity, participants will receive an individual identification code for completing the questionnaires, for data storage, and for statistical analysis. Identification codes are stored on hard copies accessible only to the study administrators. The data gathered via unipark will be downloaded and included in the final SPSS data file.

### Statistical analysis

The primary outcome measure is pre-post (i.e., T0–T2) changes on the QIDS-C. Intention-to-treat analyses will be employed in this trial. For the statistical analysis of the primary outcome we will use a three-factor mixed-design ANOVA with two two-level between-subjects factors (treatment and CTQ-based stratifier) and a two-level within-subjects factor (time, T0 and T2) in the model. For our primary outcome, the group difference at T2, we will use a model with an interaction of treatment by time. An additional analysis including T1 will be performed using planned contrasts to examine changes in depression after group and individual treatment. We will use a repeated measures MANOVA including a time by treatment interaction to assess the effects of secondary outcomes, which we assume to be moderately inter-correlated, followed by univariate repeated measures analyses.

An intended aim was to detect mechanisms of change, which requires a mediation analysis. However, mediation analyses using structural equation analyses and latent growth curve analyses require a larger sample size, more measurement occasions of potential mediators than given in our study, and the control of confounding variables between mediators and outcome [88]. Therefore, exploratory regression analyses using pre-post differences in primary and secondary outcome after the meditation group treatment and the individual treatment will be performed to detect possible candidates for mediation analyses within future studies. Missing data will be handled using multiple imputation procedures. Data collected about adverse events and serious adverse events will be summarized by type and frequency, and regression analyses will be conducted to explore relations between adverse events and treatment. For statistical analysis, the computer program SPSS® (Statistical Package for Social Sciences, version 25) will be used.

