### Childhood trauma and persistent chronic depression

A large body of research [49–52] indicates that childhood trauma or childhood adversity are risk factors for the development of PDD. Chronic depression was also significantly associated with a greater lifetime traumatic load and a higher prevalence of PTSD [7]. In a recent German study with *N* = 349 chronically depressed patients [53], 76% of the participants reported clinically relevant histories of traumatic experiences in childhood on at least one scale of the Childhood Trauma Questionnaire (CTQ). In this study the multiplicity of traumas in childhood was the strongest predictor of symptom severity, with emotional abuse and sexual abuse being the strongest predictors. This is consistent with findings that patients with a more persistent rather than episodic course of depression were significantly more likely to have suffered from childhood emotional abuse or neglect [39]. Differences in the individual history of childhood maltreatment in patients with PDD may influence the individual etiology and require special treatment elements. There is evidence that schema therapy may be effective in treating dysfunctional cognitive, emotional, and behavioral patterns due to early negative experiences [54]. Schema therapy is largely overlapping with CBT, including techniques of cognitive restructuring and behavioral activation, but adds interventions that focus on processing early maladaptive experiences and enhancement of healthy adult functioning. Therefore, to overcome stressful memories of adverse childhood experiences and the resulting dysfunctional schemas, we will also incorporate techniques of schema therapy as an option into our treatment.

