### Sample size

Previous within-group design studies [35, 38] showed moderate to large pre-post effect strengths of the group meditation program. The expected effect size for wait-list controlled studies cannot be derived from within-group design studies. However, given the expectations that a wait-list control group of patients with chronic depression will not change over the waiting period, and that the additional individual treatment component may increase the efficacy of the group meditation treatment, we assume at least a moderate effect of f = 0.25 in comparison to the wait-list control group. A power analysis was computed using G-Power 3.1.9.2 [56], with repeated measures ANOVA (within–between interaction) with two measurement time points, a power of 0.80, a strict α error probability of 0.01, and a correlation among the repeatedly measured dimensions of r = 0.7 [57], resulting in a sample size of 34 (using effect size specification as in SPSS). Hence, including a supposed drop-out rate of 25%, at least 46 patients must be recruited for this study. In order to realize group treatments with traditional group sizes (8–12 participants), we decided to perform the trial with two rounds or *cohorts* with equal size, each with one treatment and one wait-list control group. During the first round of the trial, half of the participants (cohort 1) will be recruited, randomized, and receive treatment or be in the wait-list control group. This procedure will be repeated in the second round with the second half of the participants (cohort 2). As a result, we will have a total of four therapy groups (two times one treatment and one control group). Since we strive for balanced therapy group sizes, we will include 12 participants per therapy group, i.e., 4 × 12 = 48 participants in total.

We would like to mention that as a result of this procedure we will have a stratification variable “cohort”. Since this stratification variable will be included only for administrative reasons, we will not include it in our statistical models [58].

An additional power analysis with the same parameters as above but with three measurements (including intermediate measurements), four groups (including a two-level stratification variable), and a less strict α error probability of 0.05 resulted in a sample size of 28.

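### The primary treatment-by-time ANOVA is a valid change-score test, but ANCOVA would cut its variance by about 12–15% at the plan's r = 0.7, assuming equal SDs

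*Protocol article*

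**What the plan says.** The Statistical analysis section of the protocol article first defines the outcome: "The primary outcome measure is pre-post (i.e., T0–T2) changes on the QIDS-C". The model is a "three-factor mixed-design ANOVA with two two-level between-subjects factors (treatment and CTQ-based stratifier") with "a two-level within-subjects factor (time, T0 and T2) in the model". The test is then fixed: "For our primary outcome, the group difference at T2, we will use a model with an interaction of treatment by time". No baseline covariate is named, and ANCOVA appears only in the list of abbreviations.

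The Sample size section powers the trial "with repeated measures ANOVA (within–between interaction) with two measurement time points". It says "we assume at least a moderate effect of f = 0.25 in comparison to the wait-list control group" and takes "a correlation among the repeatedly measured dimensions of r = 0.7", with α = 0.01 and power 0.80. The result is 34 evaluable patients, at least 46 recruited at 25% drop-out, and 48 planned.

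Two other statements bear on the point. The Outcome measures section says that baseline is measured after randomization, when participants already know their allocation. The Blinding section says that the authors, who are not blinded, will run the analyses.

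**The concern.** With two time points, the treatment-by-time interaction equals the group difference at T2 minus the group difference at T0. It is a comparison of change scores, and it subtracts the baseline with a slope of exactly 1. With equal SDs and r = 0.7, the regression of T2 on T0 has a slope of 0.7, so a fixed slope of 1 over-corrects and leaves avoidable noise.

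The section also names its target in two ways, as the change and as the group difference at T2. ANCOVA estimates the baseline-adjusted difference at T2 directly, with the slope taken from the data. At stake is precision in a small trial tested at a strict α, using a baseline value that is collected anyway.

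**Working it through.** **Inputs.** From the Sample size section: f = 0.25, r = 0.7, α = 0.01, power 0.80, two groups, m = 2 time points, N = 34 evaluable, 48 planned, 25% drop-out (48 × 0.75 = 36). Assumption: equal SDs at T0 and T2, since the article gives none. This is varied in step 5.

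**1. The plan's own figure.** For the within–between interaction, λ = f²·N·m/(1 − r) = 0.0625 × 2/0.3 × N = 0.4167·N, with 1 and N − 2 df. This gives N = 32 (power 0.808), and power 0.839 at N = 34. With N − 2 in place of N in λ, the answer is exactly 34 (power 0.812). Drop-out: 34/0.75 = 45.3, so 46. The stated figures reproduce, as a calculation for the planned test.

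**2. The effect this implies.** For a change-score test of a difference of d SD, λ = d²·N/(4 × 2(1 − r)) = d²·N/2.4 = 0.4167·d²·N. Setting this equal to step 1 gives d = 1.0, so the plan's inputs imply a 1.0 SD between-group difference in change.

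**3. Variance per patient, in units of SD².**
- Change score: 2(1 − r) = 2 × 0.3 = 0.60
- ANCOVA: 1 − r² = 1 − 0.49 = 0.51
- Ratio: 0.51/0.60 = (1 + r)/2 = 0.85, a loss of 15%. Since 1/0.85 = 1.176, the change score needs 17.6% more patients for equal precision.
- Other correlations: the loss is 25% at r = 0.5, 20% at 0.6 and 10% at 0.8.

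**4. Small-sample cost of estimating the slope.** Multiplying the ratio by (N − 3)/(N − 4) allows for chance baseline imbalance:
- N = 34: 0.85 × 31/30 = 0.878 (net loss 12%)
- N = 36: 0.85 × 33/32 = 0.877 (12%)
- N = 48: 0.85 × 45/44 = 0.869 (13%)

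**5. Unequal SDs.** With k = SD(T2)/SD(T0), the change variance is 1 + k² − 2rk and the ANCOVA variance is k²(1 − r²).
- k = 0.8: 0.52 v 0.326, ratio 0.63, loss about 37%
- k = 1.25: 0.8125 v 0.797, ratio 0.98, loss about 2%

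**6. Power at α = 0.01.** For the change score, λ is as in step 2 with N − 2 df. For ANCOVA, λ = d²·N/(4 × 0.51) × (N − 4)/(N − 3) with N − 3 df.

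| True difference | N | Change score | ANCOVA |
|---|---|---|---|
| 1.0 SD (plan's inputs) | 34 | 0.84 | 0.89 |
| 1.0 SD | 36 | 0.87 | 0.91 |
| 1.0 SD | 48 | 0.96 | 0.98 |
| 0.8 SD (assumption) | 36 | 0.65 | 0.71 |
| 0.8 SD (assumption) | 48 | 0.81 | 0.87 |
| 0.5 SD (assumption) | 36 | 0.23 | 0.27 |

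Taking two further df from each model for the CTQ stratifier moves these figures by at most about 0.004.

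**7. Baseline measured after allocation is known.** Suppose that knowing the allocation shifts reports by δ between groups (equal SDs, slope 0.7).
- Shift at T0 only: the change score is biased by δ, ANCOVA by about 0.7δ.
- Shift that persists equally to T2: the change score is unbiased, ANCOVA is biased by about (1 − 0.7)δ = 0.3δ.

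**The case against.** The planned analysis is coherent. The outcome is defined as a change, the main research question asks about a greater reduction, and the sample size uses the same interaction test. With groups comparable at baseline, both analyses estimate the same effect. Under the plan's inputs ANCOVA adds only 2 to 5 power points, and the required N falls only from 32 to 30. All of this stands: the point concerns efficiency between two valid tests, not an error. It gives no reason to prefer the less efficient one.

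The post-allocation baseline is the more serious objection, because T0 is not a clean pre-randomization covariate. It stands as a limit. It does not favour the change score in general, since which analysis is more biased depends on whether the shift persists (step 7).

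A reader might infer more than the document supports:
- **That the trial is already underpowered.** Under the plan's own inputs the planned test has power 0.84 to 0.96. A shortfall appears only if a smaller effect is assumed, and at 0.5 SD ANCOVA would not rescue the trial.
- **That chance baseline imbalance passes into the change score in full.** With r = 0.7 and equal SDs, a chance T0 difference of δ carries an expected T2 difference of 0.7δ, so the change contrast is off by −0.3δ.
- **That unequal CTQ strata cost further precision through equal weighting.** The article does not say that a treatment × CTQ × time term is fitted. The statement that "76% of the participants reported clinically relevant histories of traumatic experiences in childhood" describes another sample and means at least one CTQ scale. This trial's cut-offs are not given.
- **That cohort should be adjusted for too.** The Sample size section deliberately leaves it out, and this point does not depend on it.

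**Conclusion.** The concern holds as a modest and cheaply recovered loss of efficiency. The primary test fixes the baseline slope at 1 where the plan's correlation implies about 0.7. The cost is 15% of the information in large samples and 12–13% net at this trial's size, given r = 0.7 and equal SDs at T0 and T2. Neither SD is in the article, and the loss could plausibly lie anywhere from about 2% to 37%. The gain in power is 2 to 5 points at the 1.0 SD difference implied by the plan and about 6 points if the true difference were 0.8 SD. The planned test remains valid and the sample size of 34 is consistent with it.

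**What to change.** Make the primary analysis an ANCOVA of T2 QIDS-C on treatment, with T0 QIDS-C and the CTQ stratifier as additive covariates. Report the adjusted T2 difference with its confidence interval. Keep the planned mixed ANOVA as a sensitivity analysis and show both results, because T0 is taken after allocation is known and neither analysis is fully protected. State that limitation next to the results.

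The cost is a change of analysis wording and one degree of freedom; no new data are needed. Timing matters because the analysts are not blinded: the change should be recorded and dated before they analyse the data. If they have already seen outcome results by group, ANCOVA should be reported alongside the planned test and not presented as the prespecified primary analysis.

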### Trial governance

The Trial Management Group consists of the principal investigator and the study team (two clinical psychologists and two graduate student research assistants) and will provide overall management of the study including set-up of the study, recruitment, training of independent clinical raters, providing treatment, and interpretation of results. Due to the small scale of our trial, no independent trials steering committee has been planned. Overall supervision of the trial is provided by the principal investigator. Weekly meetings of the project team are held and adherence to the study protocol is checked at regular intervals. Changes to the study protocol will be communicated to the funding source, the ethics committee, and the trial registry. No interim analysis is planned due to the small scale of the study. Therapists will be video-recorded during the group treatment sessions where participants give their consent. The treatment sessions will be supervised by the principal investigator in order to continuously ensure adherence to the study protocol. We will ask the therapists to give informal feedback and participants to give formal feedback on their experience and their acceptance of the treatment program via an anonymous paper-based questionnaire. The questionnaire consists of open-ended questions, which will be evaluated qualitatively.

### Plans to promote participant retention and complete follow-up

Once a participant is enrolled, the Trial Management Group will make every reasonable effort to keep in contact with the participant during the entire study period. If a participant expresses doubts about further participation, a personal dialogue will be offered to him or her to possibly find a way to continue participating in the study. In order to pursue participant retention during the entire study period, prior to data collection time points participants will be contacted and reminded of the upcoming data collection. No further measures (e.g., material or financial incentives) are planned to promote participant retention. If participants withdraw from treatment or are excluded from interventions due to risk or otherwise deviate from the study protocol, we will attempt to collect all planned outcome data. We will only refrain from collecting outcomes from those who withdraw fully from the entire trial.

### Adverse event monitoring

An adverse event is any untoward medical occurrence (e.g., a symptom or disorder) in a patient temporarily associated with our treatment. An adverse event does not necessarily have a causal relationship with the treatment. A serious adverse event is any untoward medical occurrence that results in death, is life-threatening, requires inpatient hospitalization, or results in persistent or significant disability/incapacity [85]. Adverse events and serious adverse events will be collected throughout the trial and will be reported regarding type and time of occurrence. Collected data will be summarized by type and frequency, and regression analyses will be conducted to explore relations between adverse events and treatment. All therapists will be informed about potential adverse effects of meditation and will be encouraged to be particularly sensitive to this issue. The participants will be informed about possible side effects of psychotherapy and of meditation, and are encouraged to report negative changes.

All therapists involved in the trial are under continuous supervision by the principal investigator and will report weekly on suicidal ideations of patients or possible increase of risk for suicidal actions. Somatic conditions are checked by physicians prior to the participation in the study. Risk of side effects is considered low, but potential treatment-related adverse events will be carefully monitored. Medication will be checked regularly by psychiatrists consulted by the participants in the trial who take psychopharmacological drugs. Patients participating in the trial are instructed to keep their medication and change only after consulting their psychiatrist.

In an emergency, immediate contact with stationary psychiatric facilities in the Frankfurt area can be made. Since the interventions will be carried out by clinical psychologists and will be supervised by an experienced therapist, any worsening of the mental health condition of the participants can be detected and met accordingly.

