## Methods/design

### Design and setting

The present study is a single-center randomized controlled trial of a combination of group meditation and individual CBT versus a wait-list control condition. Participants in the control group will receive no treatment or treatment as usual (e.g., antidepressants), but no psychotherapy during the treatment of the experimental group. A wait list control group has been included to control for unspecific expectation effects and symptom fluctuations. We strive for equal group sizes. Outcome measures will be assessed at four time points: before intervention (T0); after group meditation (T1); after individual CBT (T2); and at 6-month follow-up (T3). T3 will be assessed only in the experimental group because the waitlist condition terminates after T2. The wait list control group will be offered the MeCBT program upon completion of the waiting period and the T2 measurement. Due to this design of the study, there will be no untreated control group at the T3 measurement after 52 weeks, and follow-up effects will thus be uncontrolled and modeled using data from intervention participants only. The study is conducted at the Department of Clinical Psychology and Psychotherapy at Goethe University Frankfurt. The study protocol adheres to the Standard Protocol Items: Recommendations for Interventional Trials (SPIRIT) checklist (Additional file 1). Figure 1 illustrates the study design.

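### Adverse events are defined and watched for mainly through treatment, so the exploratory regression of adverse events on treatment is open to detection bias, probably against MeCBT

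*Protocol article*

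**What the plan says.** The Adverse event monitoring section of the protocol article gives this definition: "An adverse event is any untoward medical occurrence (e.g., a symptom or disorder) in a patient temporarily associated with our treatment". It adds: "An adverse event does not necessarily have a causal relationship with the treatment". Serious events are defined by their outcome alone: "A serious adverse event is any untoward medical occurrence that results in death, is life-threatening, requires inpatient hospitalization, or results in persistent or significant disability/incapacity". On collection it says: "Adverse events and serious adverse events will be collected throughout the trial and will be reported regarding type and time of occurrence".

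Two safeguards are tied to the people who deliver treatment. Therapists "will report weekly on suicidal ideations of patients or possible increase of risk for suicidal actions". The section's confidence that deterioration will be noticed rests on the same staff: "Since the interventions will be carried out by clinical psychologists and will be supervised by an experienced therapist, any worsening of the mental health condition" is said to be detectable. Participants are also told about side effects of psychotherapy and meditation and are invited to report negative changes.

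Design and setting describes the comparator: "Participants in the control group will receive no treatment or treatment as usual (e.g., antidepressants), but no psychotherapy during the treatment of the experimental group". The wait-list arm is offered MeCBT after T2, and T3 is assessed only in the experimental arm. Outcome measures places T1, T2 and T3 at 9, 26 and 52 weeks after baseline.

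For analysis, both Statistical analysis and Adverse event monitoring say that events will be summarised by type and frequency and that "regression analyses will be conducted to explore relations between adverse events and treatment".

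**The concern.** A between-arm comparison of harms is interpretable only if an event has the same chance of being counted in either arm. Here the definition refers to trial treatment, and the surveillance described most concretely is carried out by trial therapists. Before T2 the wait-list arm has neither. Treatment status can then influence whether an event qualifies and how closely it is looked for, and the regression uses treatment status as its explanatory variable.

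At stake is the only between-arm harms analysis in the article. An excess of events under MeCBT could be partly or wholly an excess of detection, and the regression could not tell the two apart. The protocol's own Background section describes chronic depression as carrying a higher risk of suicide, so a reader will look closely at that comparison.

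**Working it through.** The article states no adverse event rate, so there is no figure to reproduce. The check is a comparison of the text, followed by an illustration on assumed inputs.

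**Step 1: does each rule reach a wait-list patient before T2?**

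| Element | Reaches the wait-list before T2? |
|---|---|
| Adverse event definition | Not on a literal reading; the next sentence drops causality but keeps the link to treatment |
| Serious adverse event definition | Yes; treatment is not mentioned |
| Collection throughout the trial | Yes as to period; it does not widen the definition or state how events are elicited |
| Weekly therapist reports on suicidality | No trial therapist in this period |
| Detection of worsening by those delivering treatment | No trial therapist in this period |
| Participants reporting negative changes | Not limited by arm, but framed around side effects of psychotherapy and meditation |
| Daily electronic questionnaire (Interventions) | Unclear; it covers mood and meditation and feeds back to the therapist |
| Assessments at T0, T1, T2 (Blinding) | Same timing for all in a cohort; the article does not say that adverse events are asked about there |

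On a literal reading, a wait-list patient's hospitalisation would be a serious adverse event without being an adverse event. The two definitions do not fit together.

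**Step 2: direction and possible size.** Let the true risk be p in both arms, with detection d1 under MeCBT and d2 on the wait-list.

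- Observed risk ratio = (p × d1)/(p × d2) = d1/d2.
- Observed odds ratio = [p·d1/(1 − p·d1)] / [p·d2/(1 − p·d2)].

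The 24 per arm comes from Sample size (48 in total, equal groups). The values p = 0.30, d1 = 0.9 and all values of d2 are assumptions. At d2 = 0.45, for example, the observed risks are 0.27 and 0.135. The risk ratio is 0.27/0.135 = 2.0 and the odds ratio is (0.27/0.73)/(0.135/0.865) = 2.37.

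| d2 | Expected events (MeCBT v wait-list) | Risk ratio | Odds ratio | Chance of a nominal 5% signal against MeCBT |
|---|---|---|---|---|
| 0.9 | 6.5 v 6.5 | 1.00 | 1.00 | 0.03 |
| 0.7 | 6.5 v 5.0 | 1.29 | 1.39 | 0.07 |
| 0.45 | 6.5 v 3.2 | 2.0 | 2.37 | 0.21 |
| 0.2 | 6.5 v 1.4 | 4.5 | 5.79 | 0.50 |

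The last column uses a normal approximation for two proportions with a two-sided 5% test. It counts signals in one direction only, which is why equal detection gives about 0.03. It also depends on p: at d2 = 0.45 it is 0.09 for p = 0.1 and 0.37 for p = 0.5. The risk ratio does not depend on p.

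**Step 3: follow-up.** Experimental patients are followed to week 52, and the wait-list condition ends at week 26. If all recorded time were counted, exposure would differ by 52/26 = 2, on top of any difference in detection. The article does not state the window for the regression.

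**The case against.** The other side has substantial points, and several stand.

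- A reader might infer that wait-list events will hardly be recorded at all. The text does not support that. Collection is stated for the whole trial, the serious-event definition is neutral, self-report is open to all participants, and the retention section promises contact with every enrolled participant. An example with no wait-list capture (7/24 v 0/24, Fisher p = 0.0094) is arithmetically correct, but it is an extreme case on an assumed 30% risk.
- A reader might take weekly therapist reports as the adverse event collection route, or picture the treated arm as seen weekly. The article describes those reports only for suicidality, and the individual sessions are fortnightly.
- A reader might infer that worsening in untreated patients would be hidden. It would not be: the blinded QIDS-C and the self-rated BDI-II are taken in both arms, so worsening still present at T1 or T2 would show there.
- A reader might call the regression biased as a matter of fact. It is exploratory, and its comparator and window are not stated. Operational detail on event collection may sit in the full protocol, which is not shown.
- The definition's adverb is probably a slip for a word about time. That does not remove the tie to treatment.

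The concern that survives does not depend on missing detail. The definition, the therapist-based surveillance and the regression on treatment are all written down, and followed as written they give unequal ascertainment by arm.

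**Conclusion.** The concern holds in a limited form. As written, the adverse event definition does not cover wait-list patients before T2, and the active surveillance described runs through therapists they do not have in that period. The exploratory regression of adverse events on treatment is therefore open to detection bias. The likely direction, making MeCBT look less safe, follows from the text. The size does not, because the documents give no event or detection rates. On the assumed inputs, spurious risk ratios run from 1.29 to 4.5; at the mild end the chance of a false signal is 0.07, against 0.03 with equal detection. A further factor of 2 in exposure arises only if the comparison is not cut at T2. The primary outcome is not affected.

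**What to change.** 1. Define an adverse event as any untoward occurrence from randomisation onward in either arm, whatever its relation to treatment, so that it agrees with the serious-event definition.
2. Ask identical adverse event questions in both arms at T1 and T2 through the online platform already used for self-report. This keeps the observer raters out of the process and protects their blinding.
3. Limit the between-arm regression to events obtained that way up to T2, which gives both arms the same window.
4. List therapist-reported events separately, labelled as treatment-arm only.

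If those visits have passed, limit the between-arm comparison to serious events ascertainable in both arms up to T2, report other events descriptively, and state the unequal ascertainment as a limitation. The Trial status section makes this likely. Recruitment ended on 4 April 2019 and completion is expected in July 2020. If the last week-52 visit falls by then, the last baseline was no later than about July 2019 and the last T2 no later than about January 2020, the month of publication. Cohort 2's baseline date is not given.

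The cost is a wording change plus one short item set, or an analysis restriction alone. The downside is fewer events in the comparison, and under the fallback no between-arm comparison of non-serious events.
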